## Abstract

**Background:**

Calcific tendinitis of the shoulder (CT) is a common disorder with a large disease burden. The initial treatment is with conservative measures. However, when this fails the next step treatment remains unclear. Minimal invasive treatment modalities have emerged. Needle aspiration of the calcific deposits (NACD) and extracorporeal shock wave therapy (ESWT) have both shown good clinical results. Nonetheless, in the current orthopedic literature there are not any studies available that compare both the effectiveness and cost-effectiveness of those two treatment modalities. Therefore, our primary objective is to compare the effectiveness of NACD to ESWT. A secondary objective is to compare the cost-effectiveness of both treatment modalities and workability.

**Methods:**

Following a power calculation using the minimal clinical important difference of our primary outcome (Constant-Murley score, CMS) 140 patients will be included in the study. Enrolment is based upon strict inclusion/ exclusion criteria outlined in the Methods section. Participants will be randomized by computer in two groups (e.g. 70 patients will receive NACD and 70 patients will receive ESWT). The NACD treatment will consist of a sonographically guided removal of the calcific deposits and the ESWT treatment will be a focused ESWT. Both treatments will be conducted according to a standardized protocol, as part of care as usual in our hospital. The primary outcome will be the between group differences in functional outcome (measured with the CMS) between baseline and after 12 months follow-up. Secondary outcomes will be questionnaires regarding the clinical outcome (SST) and quality of life (EQ-5D-5L). Furthermore, NRS pain and cost related questionnaires (iPCQ and ProDisQ) will be collected during follow-up after two months, six months and at final follow-up after 12 months.

**Discussion:**

This study will provide more insight regarding treatment for conservative therapy resistant calcific tendinitis of the shoulder by comparing NACD to focused ESWT, which will aid the physician and patient in determining the appropriate treatment plan.

**Trial registration:**

Dutch trial register: NTR7093 registered on 11 March 2018.

## Background

Calcifying tendinitis (CT) of the shoulder is a common disease of the rotator cuff in which calcium particles are deposited in one or more tendons of the rotator cuff. This can result in a typical pattern of pain, impairments in daily living and decreased range of motion. This disease mainly affects individuals between 30 and 60 years of age and females are more often affected by this condition [1–6]. The etiology of CT of the shoulder is still a matter of dispute. Several hypothesis have been postulated including a degenerative hypothesis, repetitive microtrauma, tenocyte necrosis, reactive and endochondral ossification. All leading to a postulated same end point in which that a locally decreased oxygen tension or hypoxia initiates the formation of the calcific deposit [2].

Initially, the treatment consists of conservative measures such as anti-inflammatory drugs, ice-therapy, physical therapy and/or corticosteroid injections [2, 7–10]. However, if this conservative treatment fails additional treatments must be considered. Historically, the next step treatment has been a surgical procedure [1]. However, other –less invasive– treatment modalities such as needle aspiration of the calcific deposits (NACD) and focused extracorporeal shockwave therapy (ESWT) have emerged. Over the past years both minimal invasive treatments have proven to be effective therapeutic options [9, 11–13]. NACD showed promising results mainly in non-comparing studies [14]. In addition, ESWT has also been proven to be effective, especially high-energy ESWT [11]. Although in the available orthopedic literature both treatment methods seem to be viable options, evidence comparing both treatment methods is limited [15]. Two randomized controlled trials (RCTs) have evaluated and compared the effectiveness of NACD compared to ESWT. In 2014, a RCT was published in which radial shock wave therapy was compared to NACD [16]. However, radial shock wave therapy have been shown to be less effective than focused ESWT and therefore this comparison different from the current study [13]. In 2020, the most recent RCT was published. Louwerens et al [15] compared a protocol of ESWT with four sessions of high-energy focused ESWT to ultrasound guided NACD. Both studies showed that both treatment modalities were effective in treating calcifying tendinitis of the shoulder with low complication rates. However, both studies used markedly different treatment protocols compared to the current study [15, 16]. Therefore, the exact place of NACD or ESWT in the treatment paradigm of CT is not clear yet [10].

Besides, there is very limited evidence available about the cost-effectiveness of any intervention of CT of the shoulder. As far as we are aware, only Haake et al. [7] published results concerning the cost-effectiveness of the treatment of CT. They found that ESWT costs society €1.750 to € 3.500 as a results of being unfit to work compared to €9.710 to €19.440 after surgical treatment for therapy resistant CT of the shoulder. However, there is no data available about the comparison between the minimal invasive techniques (e.g. NACD vs ESWT) [7].

Therefore, this randomized controlled trial (RCT) has several objectives. The primary objective is to compare the short and midterm effectiveness of NACD and ESWT as treatment options for conservative therapy resistant CT to define a preferable minimal invasive treatment. The hypothesis is superiority of either NACD or ESWT regarding functional outcome after 12 months. The secondary objective is to compare the cost-effectiveness of both minimal invasive techniques.

## Methods

### Study design

The design of the current study is a single center open-labeled RCT. Patients will be randomized to receive either NACD or ESWT as treatment for conservative therapy resistant CT of the shoulder (Fig. 1). All patients will be followed for 1 year. The trial was approved by the local medical and ethical commission (METC) on 16^th^ of February in 2018 (NL60762.015.17) and is registered in the Dutch trial register (NL5527/ NTR7093). Amendments were made and approved by the METC.

**Fig. 1 Fig1:**
[figure not shown]
SPIRIT-Flowchart

### Objectives

#### Primary objective

To compare the effectiveness of NACD and ESWT in patients with conservative therapy resistant CT of the shoulder over a period of 12 months. The hypothesis is superiority of either NACD or ESWT in functional recovery based on improvement of the Constant Murley Score (CMS) over a period of 12 months (superiority design).

#### Secondary objectives

To assess group differences in change scores on pain and quality of life between baseline and 12 months follow-up, and differences between groups with respect to adverse events and the use of medications in 12 months follow-up.To assess and compare the cost-effectiveness of both interventions over a period of 12 months.

### Setting

The study will be carried out at the outpatient department of orthopedic surgery and trauma of the Máxima Medical Center in the Netherlands. This is a large regional hospital equipped with a training-program for residents in orthopedic surgery. The upper extremity group consists of three experienced orthopedic surgeons.

### Population

Patients with chronic (> 6 months) shoulder complaints, calcifications visible on conventional X-rays and who did not respond to conservative, non-operative therapy for at least three months are eligible for inclusion the study. Further in/exclusion criteria are listed in Table 1.

**Table 1 Tab1:** In- and exclusion criteria

Inclusion criteria	Exclusion criteria
Age: > 18 years	ESWT or NACD treatment during the last 6 months
Chronic shoulder complaints (> 6 months)	Any contra-indication for the specific treatments (e.g. coagulopathies, malignancies in treated area)
Calcifications visible on conventional radiographs - type I or II calcifications according to the Gärtner classification minimal diameter of 10 mm	Clinical signs of a frozen shoulder or adhesive capsulitis
Able and willing to comply to study protocol	Operations of the affected shoulder in medical history
	Clinical and radiological signs of acute subacromial bursitis
	Full-thickness lesion of the rotator cuff tendon(s) on sonography
	Clinical and radiological sign of acromioclavicular osteoarthritis
	Rheumatoid arthritis or fibromyalgia
	Other intra articular pathology: cartilage lesions, biceps pathology

### Recruitment

All patients are seen and screened for in/exclusion criteria by an experienced shoulder surgeon. If the patient is eligible for inclusion a patient information form is given to the patient and an appointment is made at the specifically for this study created consultation hour. During this consult the eligibility is verified, further information about the study is giving, and after consent the patient will be included and randomized by a researcher. Furthermore, the baseline measurements are assessed and the subject screening and enrollment log filled in.

### Randomization, blinding and treatment allocation

After consent, eligible patients will be randomized and allocated to a treatment group (e.g. either NACD or ESWT) by a computer-generated randomization list using Research Manager (Research Manager, Cloud9 Software, Deventer, The Netherlands). The patients and outcome assessors will not be blinded during the study.

### Treatment of subjects

#### Group NACD

The NACD treatment aims to remove the calcific deposits in the rotator cuff and will be guided by sonography. The procedure will be performed by an experienced musculoskeletal radiologist.

For this procedure the patient will be placed in a supine position with the affected arm towards the radiologist. The skin will be disinfected. Analgesics to the skin, the subacromial bursa and cuff will be administered (Lidocain HydroCloride 1%). Under ultrasound guidance a needle (18 gauge) will be placed in the calcific deposits to fragment these under vacuum. In case of clogged needles during treatment, multiple needles can be used. After the completion of the procedure 40 mg Kenacort will be injected in the subacromial bursa as well under ultrasound guidance.

#### Group ESWT

The ESWT treatment consists of a single session of focused ESWT and aims to fragment the calcific deposits and initiate the resorption phase of calcifying tendinitis. The calcific deposits will be marked sonographically on the patient’s skin with the patient in the exact same sitting position as he/she will receive the focused ESWT. After disinfection of the skin, 1000 pulses focused ESWT with an energy flux density (EFD) of 0.15 mJ/mm^2^ will be applied targeted at the skin marks.

### Rehabilitation after intervention

Both treatment group will receive the rehabilitation as they would have received within the care as usual for CT. This means that after the treatment patients will be instructed to perform pain based movements of the affected arm. The usage of a sling is not standardized. Patients will be instructed to take NSAIDs as needed. Furthermore, if necessary exercise therapy will be prescribed at the consultation two months after treatment. If other co-interventions (such as repeating the treatment procedure, cross-over to other treatment group or even surgical treatment) are necessary during follow-up it will be initiated by the treating orthopedic surgeon.

Intake of painkillers (e.g. NSAIDs), additionally exercise therapy and co-interventions will be recorded in the case report form during study evaluations.

### Baseline characteristics

At baseline several characteristics will be documented, including age, gender, height, weight, body mass index, dominant side, affected side, duration of symptoms, occupations, hobbies. Furthermore, several radiological measurements will be carried out on the conventional X-ray to determine the size of the calcification, Gartner classification [17] and the affected tendon(s).

### Outcome measures

The primary outcome will be the group differences in recovery of functional outcome measured with the Constant-Murley Score (CMS) between baseline and 12 months follow- up. The Constant-Murley score (CMS) is a 100-points scale composed of a number of individual parameters. These parameters define the level of pain and the ability to carry out the normal daily activities of the patient [18]. The Constant-Murley score was introduced to determine the functionality after the treatment of a shoulder injury. The test is divided into four subscales: pain (15 points), activities of daily living (20 points), strength (25 points) and range of motion: forward elevation, external rotation, abduction and internal rotation of the shoulder (40 points). A higher score indicates higher quality of the function [18].

Secondary outcomes measures will be extensive and include the Numeric Rating Scale (NRS) for pain, EQ-5D-5L and simple shoulder test (SST). The NRS assesses pain intensity using a 0–10 ranking scale in which 0 represents “no pain” and 10 “unbearable pain” [19]. EQ-5D is a standardized instrument to measure of health-related quality of life. It consists of the EQ-5D descriptive system and the EQ visual analogue scale (EQ VAS). The descriptive system explores five dimensions: mobility, self-care, usual activities, pain/discomfort and anxiety/depression. The EQ VAS records the patient’s self-rated health on a vertical visual analogue scale, where the endpoints are labelled ‘The best health you can imagine’ and ‘The worst health you can imagine’. The VAS can be used as a quantitative measure of health outcome that reflect the patient’s own judgement [20]. The SST is a patient reported outcome measurement (PROM) in which a score between 0 and 100 can be calculated based on a 12-item long questionnaire [21]. Zero represent the worse shoulder function and 100 a perfect shoulder function. Besides these outcome measures adverse events, co-interventions and co-medications will be monitored during follow-up. Furthermore, the IMTA Productivity Cost Questionnaire (iPCQ) [22] and PROductivity and DISease Questionnaire (PRODISQ) [23] are included to evaluate the cost-effectiveness. The extensive data collection schedule is outlined in Table 2.

**Table 2 Tab2:** Data collection schedule

**Range**	**Baseline** **T = 0**	**8 weeks** **post-intervention**	**6 months** **post-intervention**	**12 months** **post-intervention**
		± 1 week	± 2 weeks	± 4 weeks
Demographic Information	✓			
Historical records	✓			
Sonography	✓			
HADS	✓			
PCS	✓			
CMS	✓	✓	✓	✓
NRS	✓	✓	✓	✓
EQ-5D	✓	✓	✓	✓
SST	✓	✓	✓	✓
iPCQ	✓	✓	✓	✓
ProDisq	✓	✓	✓	✓
X-rays	✓	✓		✓
Used co-medication		✓	✓	✓
Adverse Events		✓	✓	✓

### Data management

All data will be handled confidentially and is pseudonymized in compliance with the Dutch Personal Data Protection Act. All patient reported outcome measures are collected digitally and all patient data will be stored coded using data management software (Research Manager, Cloud9 Software, Deventer, The Netherlands). Each patient gets a unique study number which is used in all documents regarding the study. Access to the randomization key is restricted to the study-team. The local METC will be annually informed regarding rates of inclusion, adverse events and study results. The local METC graded the study as a ‘low risk’ study. A monitoring plan will be carried out by an external party during execution of the study.

### Statistical analyses

The primary analyses will be performed according to the ‘intention to treat’-principle, indicating that participants will be included in the analysis according to the by randomization allocated group. Secondary analyses will be limited to the compliant participants, independent of which intervention they were randomized (per protocol analysis). Distribution analysis of all variables will be tested by the Shapiro–Wilk test.

Primary outcome will be analyzed by linear regression analyses with change in CMS between baseline and 12 month follow up as dependent variable. The assumptions of constant variance and linear relationships will be assessed using scatter plots. Should any of these assumptions seriously fail then variable transformations will be used. Analyses will be adjusted for baseline variables that change the effect estimate with more than 10%. Similar analyses will be performed for the secondary continuous outcome parameters. Differences between groups on complications and additional treatment will be analyzed by means of Mann–Whitney tests. Furthermore, differences in recovery trajectories between groups will explored by means of mixed ANOVA. Statistical analyses will be performed using SPSS software (IBM, USA). An alpha level of 0.05 will be accepted as significant.

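### The 10% change-in-estimate rule leaves baseline CMS out of the primary model as a fixed term and ties the choice of covariates to the observed treatment effect; the cost is modest and the remedy is one sentence

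*Protocol article*

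**What the plan says.** All of this is in the Methods of the protocol article.

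- **Model** (Statistical analyses): "Primary outcome will be analyzed by linear regression analyses with change in CMS between baseline and 12 month follow up as dependent variable". No covariate is named as a fixed term.
- **Adjustment rule** (same section): "Analyses will be adjusted for baseline variables that change the effect estimate with more than 10" per cent. This is the only statement on adjustment.
- **Reach** (same section): "Similar analyses will be performed for the secondary continuous outcome parameters". The rule therefore extends to the secondary continuous outcomes.
- **Assumption checks** (same section): "Should any of these assumptions seriously fail then variable transformations will be used".
- **Possible candidates** (Baseline characteristics section of the article): "At baseline several characteristics will be documented, including age, gender, height, weight, body mass index, dominant side, affected side, duration of symptoms, occupations, hobbies". Radiological measures follow, and Table 2 adds baseline questionnaires. Table 2 also schedules CMS at baseline for every patient.
- **Allocation** (Randomization, blinding and treatment allocation): patients are allocated "by a computer-generated randomization list using Research Manager", with no stratification on CMS stated. On blinding: "The patients and outcome assessors will not be blinded during the study".

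**The concern.** A change-in-estimate screen is a tool for confounding in observational data. Under randomization there is no systematic confounding to remove. Whatever moves the estimate is chance imbalance in a variable related to the outcome.

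Two consequences follow.

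1. The threshold is a fraction of the treatment estimate. With an estimate of 1 point, a shift of 0.1 point on a 100-point scale brings a covariate in. With an estimate of 8.6 points the shift must exceed 0.86. The same variable with the same imbalance can be in or out depending on how large the effect looks, so the model cannot be written down before outcomes are compared by arm.
2. Baseline CMS is part of the change score and is measured in everyone. Its value as a covariate is precision, which does not depend on imbalance. The rule admits it only when imbalance is large enough, so precision from data already collected is sometimes given up.

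At stake are the width of the primary interval and whether the primary model can be shown to have been fixed in advance, in a trial where patients and assessors know the allocation.

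**Working it through.** **Inputs from the article:** SD 17.2, target difference 8.6, power 80%, alpha 0.05, 63 per group, 10% dropout, MCID 10.4 (Sample size calculation); 1:1 allocation (Abstract). **Assumed, because the article does not give them:** correlation ρ between baseline and 12-month CMS of 0.3, 0.5 or 0.7; equal SD at both visits; normal data; covariates screened one at a time against the unadjusted estimate, with baseline CMS among the candidates.

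**Step 1. The plan's own figures reproduce.** Two-sided, n = 2(1.960 + 0.842)²(17.2/8.6)² = 62.8, so 63 per group. For 10.4 points, n = 2(1.960 + 0.842)²(17.2/10.4)² = 42.9, so 43. Then 126/0.9 = 140. The sample size is not in dispute.

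**Step 2. Precision with and without baseline CMS.** The SD of the change score is 17.2√(2(1−ρ)). The residual SD with baseline CMS in the model is 17.2√(1−ρ²). Their ratio is √(2/(1+ρ)).

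| ρ | SD, change | SD, ANCOVA | Ratio | Power at 63/arm, change vs ANCOVA | n/arm for 80%, change vs ANCOVA |
|---|---|---|---|---|---|
| 0.3 | 20.4 | 16.4 | 1.24 | 66% vs 84% | 88 vs 58 |
| 0.5 | 17.2 | 14.9 | 1.15 | 80% vs 90% | 63 vs 48 |
| 0.7 | 13.3 | 12.3 | 1.08 | 95% vs 98% | 38 vs 33 |

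**Step 3. When does baseline CMS enter?** Adding it shifts the estimate by about (1−ρ) times the chance baseline difference, whose standard error is 17.2√(2/63) = 3.06 points. With the estimate near 8.6, entry needs a baseline difference above 0.86/(1−ρ):

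- ρ = 0.3: 1.23 points; 1.23/3.06 = 0.40; two-sided probability 69%.
- ρ = 0.5: 1.72 points; 0.56; 57%.
- ρ = 0.7: 2.87 points; 0.94; 35%.

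Simulation gives the same entry rates (69%, 57%, 35%), so baseline CMS is left out in about 31%, 42% and 65% of trials.

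With no true difference there is a closed form. Put s = √((1+ρ)/(1−ρ)) = 1.36, 1.73, 2.38. The entry probability is [arctan(11/s) + arctan(9/s)]/π = 91%, 89% and 85%, so baseline CMS is left out in 9%, 11% and 15%. Simulation, which estimates the slope, gives 16% for the last. At 4.3 points simulated entry is 84%, 77% and 63%.

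**Step 4. Average cost of the rule, with baseline CMS as the only candidate (simulation, 63 per arm).**

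| ρ | Mean SE vs ANCOVA, at 8.6 | Mean SE vs ANCOVA, at 0 | Power at 8.6, rule vs ANCOVA |
|---|---|---|---|
| 0.3 | +7% | +2% | 80% vs 83% |
| 0.5 | +6% | +2% | 87–88% vs 89% |
| 0.7 | +5% | +1% | 97% vs 97% |

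Rejection with no difference was 4.0% to 4.6% and coverage 95% to 96%. In trials at 8.6 points where baseline CMS was left out, the estimate differed from ANCOVA by 0.4 to 0.5 points on average.

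**Step 5. More candidates.** With eight further candidates, each assumed to correlate 0.2 with 12-month CMS, the mean number of covariates selected was 5.8 to 6.8 at no effect and 1.9 to 2.5 at 8.6 points. The model thus changes with the effect seen. Rejection with no difference was 2.7% to 4.0%.

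**The case against.** The case for leaving the rule alone is substantial, and most of it stands as a limit on severity.

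- **A reader might infer a false-positive problem.** The checks do not support that. Applied mechanically, the rule rejected at or below 5% in the settings above. Across one-at-a-time and stepwise versions with ten other candidates the range was 3.7% to 5.8%.
- **A reader might take 24%, 15% and 8% as the price of the rule.** Those figures apply only to trials in which baseline CMS is left out. The average price is 5% to 7% in standard error at 8.6 points and 1% to 2% at no difference. Omission is also most frequent where it costs least: at ρ = 0.7 the power loss is under 1 point.
- **A reader might conclude that baseline CMS would seldom be used.** With a small or null effect it enters in most trials.
- **The rule can gain precision.** With eight prognostic extras its simulated power at 8.6 points was 87%, 94% and nearly 100%, above ANCOVA on baseline CMS alone. That gain comes from the prognostic value of the extra variables, which naming them in advance would also secure.
- **The transformation sentence might be read as licence to log or square-root the change score, which can be negative.** The text does not say this. It speaks of variables, names no transformation, and applies only on serious failure. With a binary group, linearity concerns continuous covariates, and transforming those leaves the treatment coefficient in CMS points. Transforming the outcome is only one possible reading.
- **The article is condensed.** The absence of a candidate list is therefore not held against it. The rule itself is stated, so it can be judged.

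**Conclusion.** The point holds at modest size. The article fixes a selection rule for its primary model that has no confounding to correct, depends on the treatment estimate, and does not guarantee baseline CMS a place. The harm is a modest average loss of precision and a primary model that depends on the data. At 8.6 points the power loss is about 3, 2 and under 1 points for ρ = 0.3, 0.5 and 0.7, with no inflation of type I error and no loss of coverage. It is a low-cost improvement and not a critical error.

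The omission rates and losses rest on the assumed correlations, equal SDs, normality and the one-at-a-time reading. That the threshold scales with the estimate, and that no covariate is fixed, does not depend on them.

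**What to change.** Replace the adjustment sentence with text to this effect: the primary analysis is a linear regression of change in CMS on randomized group, with baseline CMS as a covariate in every case. Then:

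- Name any further covariates now, before any further outcome data by arm are examined. Waiting until database lock is weaker protection here, because assessors are unblinded and the Data management section gives the study team access to the randomization key.
- Use each secondary continuous outcome's own baseline value in the same way.
- Drop the 10% rule or confine it to a labelled sensitivity analysis.
- As a minor addition, keep the primary outcome in CMS points so that the result can be set against 8.6 and 10.4, and use heteroscedasticity-consistent (HC3) standard errors if variance is unequal.

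The cost is a wording change. It needs no new data or patients, and the planned 63 per group exceeds the 58, 48 and 33 needed with baseline CMS fixed.

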### Sample size calculation

For the sample size calculation, we used the minimal clinically important difference (MCID) for the Constant Murley Score as determined by the study of Kukkonen et al [24].

The reported MCID over a period of 12 months was 10.4 points, with a mean Constant Murray Score of 53.1 (standard deviation of 17.2) at baseline [24].

We aim to find a superiority of one of the two treatment options to treat patients with calcifying tendinitis of the shoulder. Our hypothesis is that superiority of NACD or ESWT above the other treatment in functional recovery over a period of 12 months will be found. Superiority will be expressed by an additional effect size of minimally 0.5. Using a standard deviation of 17.2 of the CMS, we aim to detect a minimally difference of 8.6 points between both groups. Using a power of 80% and an alpha of 0.05 the required sample size is 63 patients per group, resulting in a total of 126 patients. With this number of patients, we will also able to detect a MCID between both groups of 10.4 points (required number of patients is 43 per group). The final sample size required is 140 patients, to accommodate 10% potential dropout rate over 1 year.

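### Complications and additional treatment are compared only by Mann–Whitney tests, which give no risk difference, ratio or confidence interval for a stated secondary objective

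*Protocol article*

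**What the plan says.** The Statistical analyses section of the protocol article states: "Differences between groups on complications and additional treatment will be analyzed by means of Mann–Whitney tests". It names no effect measure and no interval for these outcomes. In the same section the primary outcome and the continuous secondary outcomes go to linear regression, which does give a between-group difference. The significance level is general ("An alpha level of 0.05 will be accepted as significant") and the software is SPSS. The section does not say whether asymptotic or exact p-values will be used.

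The Secondary objectives include assessing "differences between groups with respect to adverse events and the use of medications in 12 months follow-up". Additional treatment is not named there. The section on rehabilitation gives its content: exercise therapy if needed, and co-interventions such as a repeat of the procedure, cross-over to the other treatment, or surgery. Under Outcome measures, adverse events and co-interventions are simply monitored, with no score or scale. The Background reports that in two earlier trials both treatments were "effective in treating calcifying tendinitis of the shoulder with low complication rates".

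**The concern.** A Mann–Whitney test compares the ranks of ordinal or continuous values. Whether a patient had a complication, a repeat procedure or an operation is an event, recorded as yes/no or as a small count. Ranking such data produces almost nothing but ties. The test then only compares two proportions, without reporting either their difference or its precision.

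This matters because the trial wants to identify a preferable treatment and to inform shared decisions. If complications are as uncommon as in the earlier trials, a comparison of 70 with 70 will probably be non-significant whatever the truth. A p-value alone does not tell the reader how large an excess risk the data still allow.

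**Working it through.** **Inputs.** Arm size 70 (Abstract, Methods: "70 patients will receive NACD and 70 patients will receive ESWT"); alternative size 63 per arm (Sample size calculation); alpha 0.05, taken as two-sided because superiority of either arm is the hypothesis. No event rate is given beyond low in earlier trials, so rates from 0.1% to 50% were examined. Yes/no coding is an assumption.

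**Step 1: the plan's own figures.** With SD 17.2 and difference 8.6, the effect size is 8.6/17.2 = 0.5, and n = 2(1.960 + 0.842)²/0.5² = 62.8, so 63 per group. Then 126/(1 − 0.10) = 140, or 70 per arm. Both figures reproduce. No figure is stated for complications or additional treatment.

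**Step 2: what the test becomes on yes/no data.** For a events versus b events, n per arm and N = 2n, the asymptotic tie-corrected Mann–Whitney statistic (no continuity correction), squared, is

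χ² = (N − 1)·[a(n − b) − b(n − a)]² / [n²(a + b)(N − a − b)].

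For 3 v 0 at n = 70: 139 × 210² / (70² × 3 × 137) = 6,129,900 / 2,013,900 = 3.044, p = 0.081. The Mann–Whitney and (N−1) chi-square p-values agreed to four decimals in every table tried.

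**Step 3: is the false-positive rate inflated?** For a common event rate π, the true type I error is the sum of Bin(a; n, π)·Bin(b; n, π) over all pairs (a, b) with p ≤ 0.05.

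| Event rate | Mann–Whitney, 70/arm | Fisher exact, 70/arm | Mann–Whitney, 63/arm |
|---|---|---|---|
| 1% | 0.005 | 0.0001 | 0.004 |
| 2% | 0.026 | 0.0014 | 0.021 |
| 3% | 0.041 | 0.005 | 0.037 |
| 5% | 0.048 | 0.0135 | 0.047 |
| 10% | 0.051 | 0.025 | 0.051 |
| 20% | 0.051 | 0.031 | 0.048 |

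The maximum over all rates is 0.052 at 70 per arm and 0.054 at 63 per arm (the latter near a 40% rate). With Poisson counts (mean 0.02 to 0.4 per patient, 20,000 simulated trials, 70 per arm) it was 0.025 to 0.051. There is no meaningful inflation.

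**Step 4: what the p-value leaves out.** Take 3 v 0 at 70 per arm. The risk difference is 3/70 − 0 = 4.3 points. The Wilson limits are [p + z²/2n ± z√(p(1−p)/n + z²/4n²)]/(1 + z²/n), which gives 1.47% to 11.86% for 3/70 and 0 to 5.20% for 0/70. Newcombe's limits are then:

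- lower: 4.29 − √[(4.29 − 1.47)² + 5.20²] = 4.29 − 5.92 = −1.6 points
- upper: 4.29 + √[(11.86 − 4.29)² + 0²] = +11.9 points

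So p = 0.081 is compatible with an excess of almost 12 percentage points.

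**Step 5: borderline tables, 70 per arm.**

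| Events | Mann–Whitney p | Fisher p | Boschloo p | Barnard p | Newcombe 95% CI (points) |
|---|---|---|---|---|---|
| 4 v 0 | 0.043 | 0.120 | 0.088 | 0.049 | −0.5 to +13.8 |
| 8 v 2 | 0.0498 | 0.097 | 0.076 | 0.052 | −0.3 to +18.3 |

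On which side of 0.05 such a result falls depends on the procedure chosen, and the article does not fix whether the p-value is asymptotic or exact.

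**The case against.** A reader might infer something stronger: that the planned test produces p-values that are too small when events are rare, and so declares safety differences that exact tests would not support. This is not supported. The p-values are smaller than Fisher's, but Step 3 shows that the Mann–Whitney test is itself conservative at low rates and that Fisher's test is far more so. Exact tests also disagree among themselves: for 4 v 0, Barnard's gives 0.049 and Boschloo's 0.088. An exact Mann–Whitney p-value, which the article does not rule out, would be a conditional exact test on yes/no data.

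Four further objections deserve weight.

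- **Coding.** Yes/no coding is inferred. If additional treatments were counted or ranked per patient, a rank test would be a defensible test, with sound size in the Poisson simulation. This stands as a limit on the point, but a rank test on counts still gives no rate ratio.
- **Condensed article.** Tabulation and intervals are often left to the full protocol or analysis plan, and nothing here says that counts will be withheld. This stands in part. The article does, however, name the method for these outcomes, and it is that choice which is questioned.
- **Rank effect.** On yes/no data the Mann–Whitney effect measure equals 0.5 plus half the risk difference, so an estimate is recoverable. That is true, but the plan does not call for it, and the risk difference is the plainer way to present it.
- **Sources.** The secondary objective covers adverse events and medication use, not additional treatment. The low complication rates come from two earlier trials with different treatment protocols and are not a forecast for this one. Both stand.

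**Conclusion.** The point holds as one about estimation. The stated analysis of complications and additional treatment amounts, on yes/no data, to a chi-square test with no effect measure or interval, and for complications it serves a stated secondary objective. The illustration is 3 v 0 at 70 per arm: p = 0.081, with an interval of −1.6 to +11.9 points that the planned analysis would not show. This assumes yes/no coding, full arms of 70 and complications being the adverse events of the objective; the event counts are illustrative because the article gives none. Type I error is not a ground for criticism (at most 0.052 at 70 per arm, 0.054 at 63). Priority is low: neither the primary analysis nor the sample size is touched.

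**What to change.** Replace the Mann–Whitney sentence. State that, by randomised arm, the number and percentage of patients with at least one complication, and with each type of additional treatment (exercise therapy, repeat procedure, cross-over and surgery separately), will be reported with a risk difference and a 95% score-type confidence interval, for example Newcombe's. If events per patient are to be compared, give a rate ratio with its interval instead. State how each outcome is coded and which p-value will be used. An exact test is acceptable but is a preference, and Fisher's is markedly conservative at low rates.

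The cost is a few lines of wording and a little extra analysis. No further data or patients are needed.
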